## Abstract

**Background:**

The population of adolescents and young adults with congenital heart disease (CHD) is growing exponentially. These survivors are at risk of late cardiac complications and require lifelong cardiology care. However, there is a paucity of data on how to prepare adolescents to assume responsibility for their health and function within the adult health care system. Evidence-based transition strategies are required.

**Methods:**

The Congenital Heart Adolescents Participating in Transition Evaluation Research (CHAPTER 2) Study is a two-site cluster randomized clinical trial designed to evaluate the efficacy of a nurse-led transition intervention for 16–17 year olds with moderate or complex CHD. The primary endpoint is excess time to adult CHD care, defined as the time interval between the final pediatric cardiology appointment and the first adult CHD appointment, minus the recommended time interval between these appointments. Secondary endpoints include the MyHeart score (CHD knowledge), Transition Readiness Assessment Questionnaire score, and need for catheter or surgical re-intervention. Participants are enrolled in clusters based on week of attendance in the pediatric cardiology clinic. The intervention consists of two one-hour individualized sessions between a cardiology nurse and study participant. Session One focuses on knowledge of the participant’s CHD, review of their cardiac anatomy and prior interventions, and potential late cardiac complications. Session Two focuses on self-management and communication skills through review and discussion of videos and role-play. The study will recruit 120 participants.

**Discussion:**

Many adolescents and young adults experience a gap in care predisposing them to late cardiac complications. The CHAPTER 2 Study will investigate the impact of a nurse-led transition intervention among adolescents with CHD. Fidelity of the intervention is a major focus and priority. This study will build on our experience by (i) enrolling at two tertiary care programs, (ii) including a self-management intervention component, and (iii) evaluating the impact of the intervention on time to ACHD care, a clinically relevant outcome. The results of this study will inform pediatric cardiology programs, patients and policy makers in judging whether a structured intervention program provides clinically meaningful outcomes for adolescents and young adults living with CHD.

**Trial registration:**

ClinicalTrials.gov ID NCT01723332

## Background

Major advances in the management of children with congenital heart disease (CHD) have evolved over the past three decades. As a consequence, over 90 % of these children reach adulthood and the population of adolescents and young adults with CHD is growing exponentially [1].However, this emerging “survivor” population has complex needs. These individuals are at risk of substantial cardiac morbidity [2, 3] and mortality [4, 5] in early-to-mid adult years. Unfortunately, 14–53 % of young adults are not successfully transferred to an adult CHD (ACHD) centre after graduating from a pediatric cardiac centre [6–8], and failure to attend an ACHD clinic results in excess cardiac morbidity [7, 9, 10]. Furthermore, adolescents and young adults with CHD have limited knowledge about their heart [11–13], limiting their ability to communicate confidently with health care providers [14].

At present there is a paucity of outcome data regarding the impact and effectiveness of CHD transition interventions*.* Indeed, there is a lack of transition outcome data for chronic pediatric conditions in general. This speaks to the urgency of developing evidence-based intervention programs that will optimize pediatric to adult health care transition using methods that can be readily adopted by clinical programs. The American Heart Association published a Scientific Statement on the subject of transition in 2011 that emphasized the relevance of this topic to the CHD community and acknowledged the lack of data on transition programming [15].

To address these knowledge gaps our team conducted the Congenital Heart Adolescents Participating in Transition Evaluation Research (CHAPTER 1) Study [16] to evaluate a single-session nurse-led transition education intervention, focusing on CHD knowledge, for youth 15–17 years of age. This study significantly improved patients’ knowledge of their CHD lesion in the intervention group at one month, which was sustained at 6 months. The intervention group also had higher self-management skills at six months, even though self-management skills were not the focus of the intervention. Limitations of this study include enrollment at a single center and use of surrogate outcomes (questionnaires) rather than participant behaviors such as attendance at an ACHD clinic. The current study was designed to build upon our experience with CHAPTER 1, specifically to include a self-management component of the intervention, to document time to first ACHD clinic appointment, and to assess generalizability of the intervention across more than one clinical program.

The primary aim of the CHAPTER 2 study is to determine the impact of a nurse-led intervention on time to first ACHD clinic attendance among youth graduating from one of two quaternary-care pediatric cardiology programs. We hypothesize that the transition intervention in combination with usual care will result in superior timing of the first ACHD clinic attendance compared to usual care alone. Secondary aims are to describe: 1) change in adolescent knowledge of their CHD, 2) change in self-management and self-advocacy skills using validated instruments [17, 18], 3) Incidence of cardiac procedures post enrollment, and 4) the frequency and content of verbal and written (email/text messaging) dialogue between nurse and participant.

## Methods

### Study design

The CHAPTER 2 Study is a two-center cluster randomized controlled trial of a nurse-led transition intervention versus usual care (see “usual care” section below). The intervention will consist of two individualized sessions lasting ~60 min each held two months apart, in or adjacent to the pediatric cardiology clinic. The study is registered with Clinical Trials.gov (ID NCT01723332) and will be conducted in accordance with CONSORT guidelines (Fig. 1) [19].

**Fig. 1 Fig1:**
[figure not shown]
CONSORT diagram

### Study setting and participants

The study will be conducted at The Hospital for Sick Children (“SickKids”, Toronto, Canada) and the Stollery Children’s Hospital (Edmonton, Canada). These are the largest pediatric cardiology programs in Canada and offer the full range of cardiology and cardiac surgical subspecialty services. We will include 16–17 year olds with moderate or complex CHD (as previously defined) [20] who have not yet been transferred to adult care. Exclusion criteria will be (i) less than a Grade 6 level of reading and comprehension, based on parent report, and (ii) heart transplantation.

### Transition intervention

The intervention will be conducted by one of two cardiology registered nurses (RNs) at each site (total 4 RNs) who are experienced working with teens. Youth will attend two one-on-one sessions with the same RN. Sessions will be youth-oriented, interactive, and engaging. Session One will occur immediately after a pediatric cardiology clinic visit to minimize study burden and to adhere with recommendations that transition interventions be delivered in clinical settings [21]. Individual sessions, in contrast to group sessions, allow the content to be patient-specific. Session Two will occur two months after Session One, in conjunction with another clinic appointment or as the sole purpose of a return visit. Individual participant flow through the study is illustrated in Fig. 2.

**Fig. 2 Fig2:**
[figure not shown]
Individual participant timeline

Immediately prior to Session One, the RN will review the cardiology chart to become familiar with the cardiac history including CHD diagnoses, names and dates of cardiac surgical procedures and cardiac catheterizations, and current cardiac medications and doses. Session One (1 h) will emphasize education; Session Two (1.0–1.5 h) will emphasize self-management. Details of each session are summarized in Table 1.

**Table 1 Tab1:** Transition Intervention: summary of characteristics and content

Characteristic	Session 1: Emphasis on Education (Held at time of enrollment)	Session 2: Emphasis on Self-management (2 months post Session 1)
Aim	To inform participants about their heart condition	To motivate participants to self-manage and selfadvocate
Approach	Didactic/educational	Experiential/engaging
Role of nurse	Teacher	Facilitator
Mechanism of change	Cognitive/learning	Behavioral/applied action
Content	a) Introduction to transition/its importance	a) Discuss education-related goal set in Session 1
	b) Discussion of confidentiality, promote trust with RN	b) Discussion of “self-management” and its relevance to health
	c) Creation of MyHealth passport, including	c) View & discuss six 1-min videos illustrating interactions between a health care provider (HCP) & young adults with poor vs. strong assertiveness skills
	- name of cardiac condition	
	- previous cardiac interventions	
	- name and purpose of medications	
	d) Review cardiac anatomy (patient-specific)	d) View & discuss “Talking with your doctor” video; review GLADD approach (Give, Listen, Ask, Decide, Do)
	e) Discussion of potential future cardiac complications (patient-specific)	e) Role-play an interaction between a HCP & the participant who practices being assertive
	f) Review names & location of local ACHD cardiologists	f) Discuss SMART goal setting (Specific, Measurable, Attainable, Realistic, Timely)
	g) Introduction to relevant websites	g) Review booklet “When You’re 18”, take home
	h) Discussion of 3 scenarios addressing alcohol, smoking/street drugs, & sexuality/contraception	h) Visit website “Health Care Transitions”
	i) Introduce youth-oriented take-home written materials	i) Encourage email or text messages with RN. Questions posed within 7 days:
		1. “What helped you the most?”
		2. “What helped you the least?”
		3. “Do you have any questions for me?”
	j) Set one education-related goal for session 2	
	k) Accompany participant to the ACHD clinic	
	l) Provide study email address; encourage emails or text messages with RN. Questions posed to participants within 7 days:	
	1. “Where is your MyHealth passport now?”	
	2. “Have you used your MyHealth passport or shown it to anyone?”	
	3. “Do you have any questions for me?”	

*ACHD* adult congenital heart disease; RN: registered nurse

### Treatment fidelity and quality assurance

Consistency of the intervention between study RNs and study participants is a priority of this study. Team education will start with an in-person two-day meeting in Toronto involving study RNs, led by the study investigator ([name]) who co-developed and conducted many of the interventions in the CHAPTER 1 study [16]. Professionally filmed video-tapes depicting Sessions One and Two were prepared for the RNs on how to conduct the sessions with a standardized patient. These teaching videos will be viewed by each study RN and role-playing will be performed for practice.

Audio recordings of sessions One and Two with study participants will be conducted if the participant agrees. Evaluation of treatment fidelity will be based on review of nursing logs and/or audiotapes by other study RNs and team members ([name], [name]). Monthly conference calls involving all study RNs will be conducted to provide feedback and discuss issues related to the intervention as they arise.

After each session the RN will complete an intervention log. The RN will record completion of each intervention component as described in Table 1, and use field notes to record the participant’s knowledge, enthusiasm, and commitment to the intervention. All intervention logs and field notes will be reviewed monthly by team members ([name], [name], and RNs), as part of ongoing quality assurance.

### Usual care

No transition program is formally in place at the Stollery site. Families receive written information about their child’s CHD, suggested timelines for increasing teens’ self-management of his/her CHD, and at the last pediatric visit a “graduation” package with information about the ACHD program is provided. At SickKids, usual care is similar. However, to account for potential differences in usual care, randomization will be stratified by site. With multiple pediatric cardiologists and clinic nurses at each site, clinician-led education is likely variable and constrained by limited clinic time. At both sites, pertinent medical records are sent to ACHD providers at the time of transfer. Both ACHD clinics send a welcome letter to patients indicating approximately when their first ACHD appointment will be. A second letter is sent one month prior to the first ACHD appointment with the date and time. Patients who do not attend are contacted by telephone to reschedule. All components of usual care will be tracked by the project coordinator at each site, and any change in usual care during the study will be documented.

### Group allocation

Participants will be randomized by clusters defined by week of attendance in the pediatric cardiology clinic. As week (not study participant) is the unit of randomization, this is a cluster randomization design. This method of randomization: 1) prevents two adolescents in the same waiting room being allocated to different groups and 2) facilitates scheduling of study RNs, who will be available at short notice to provide the intervention during intervention weeks. Cardiologists will not be informed of group assignment, preventing potential bias by cardiologist co-intervention. We anticipate enrollment of 3–4 patients per week, i.e., cluster size will be ≤ 4. To determine which weeks are “intervention weeks” vs. “usual care weeks”, a biostatistician will prepare a randomization sequence.

A 1:1 ratio of intervention: usual care weeks will be used until midway through enrollment, when there will be a re-evaluation. If there is an imbalance, then there will be an adjustment of the ratio of intervention to usual care weeks.

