### Quantitative data analysis

Intention-to-treat analysis will be used and all statistical tests will be two-sided. Baseline characteristics of the control (usual care) and intervention groups will be summarized using descriptive statistics (e.g., means, medians, standard deviations, frequencies, proportions). Kaplan-Meier plots will display excess time to first ACHD appointment by treatment group. Log-rank tests with a cluster-level bootstrap will test the difference in the excess time distribution between the intervention and control groups. The cluster sizes are likely to be 3–4. All statistical analyses will account for the cluster randomization. Participants who have not attended the ACHD clinic by the end of the study period (i.e., are censored) will still contribute to the primary outcome, as survival analysis is designed to accommodate censored data. We will assess differences in mean scores of each secondary outcome at baseline, 1, 6, 12, and 18 months, where applicable, by treatment group using general linear mixed models [24] that take both the cluster randomization and longitudinal nature of the data into account. Additional analyses will be stratified by a) study site (Edmonton versus Toronto) and b) attended first ACHD appointment (yes/no).

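### If the ratio of weeks is changed midway, arm becomes tied to enrolment phase, and the stated primary log-rank test names no stratification by phase

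*Protocol article*

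**What the plan says.** All references are to the protocol article.

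- **Group allocation.** The unit is the week: "Participants will be randomized by clusters defined by week of attendance in the pediatric cardiology clinic". A 1:1 "ratio of intervention: usual care weeks will be used until midway through enrollment, when there will be a re-evaluation". Then: "If there is an imbalance, then there will be an adjustment of the ratio of intervention to usual care weeks". No trigger, new ratio or type of sequence is given.
- **Usual care.** To allow for differences between the centres, "randomization will be stratified by site". No other stratum is mentioned. The same section says that "any change in usual care during the study will be documented", without linking this to the analysis.
- **Quantitative data analysis.** "Log-rank tests with a cluster-level bootstrap will test the difference in the excess time distribution between the intervention and control groups". Also: "All statistical analyses will account for the cluster randomization". Stratified analyses are described only as additional ones, by site and by whether the first adult appointment was attended. Enrolment phase is not among them.
- **Potential limitations.** Waiting lists and cardiologists' awareness of the study are accepted as influences on the outcome, and set aside because both groups would be affected alike.

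**The concern.** With one allocation ratio throughout, calendar time is balanced between the arms in expectation. A ratio moved in the second half to offset the first half breaks this: the arm that was ahead early is under-represented late. Anything that shifts adult-clinic attendance for everyone over enrolment, such as a change in usual care or in clinic capacity, then reaches the two arms in different proportions and appears as a treatment difference.

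The bootstrap over weeks does not remove this. It affects the standard error, whereas the association between arm and period shifts the comparison itself. The argument under Potential limitations, that system factors act equally on both groups, also relies on the arms being enrolled concurrently, which the ratio change weakens. At stake is the type I error of the primary test, in exchange for a small gain in precision.

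**Working it through.** **Planned comparison.** Proposed sample size gives 60 per group, 90% versus 70% attended, two-sided α = 0.05 and power of at least 80%.
- Hazard ratio = ln(0.1)/ln(0.3) = 1.912. Expected events = 60×0.9 + 60×0.7 = 96.
- Schoenfeld power = Φ(√96/2 × ln 1.912 − 1.96) = Φ(1.22) ≈ 88.8% before clustering. It stays at or above 80% up to a design effect of about 1.29.

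The stated power therefore reproduces, and this point does not affect it. The 20-point target is the yardstick below.

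**Assumptions (not in the article).** The first half of 60 splits 36:24; the ratio is moved so that the arms finish at 60:60, making the second half 24:36; there is no treatment effect; attendance at 24 months drifts between halves.

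**Association between arm and phase.**
- With the reversal, the late-enrolled share is 24/60 = 40% for intervention and 36/60 = 60% for usual care: a gap of 20 points.
- With the ratio left at 1:1 (second half 30:30), the shares are 30/66 = 45.5% and 30/54 = 55.6%: a gap of about 10 points.

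**Spurious difference = drift × gap.**

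| Drift | With reversal | Ratio left at 1:1 |
|---|---|---|
| 10 points (70% to 80%) | 0.10 × 20 = 2.0 points | 0.10 × 10.1 = 1.0 point |
| 20 points (60% to 80%) | 0.20 × 20 = 4.0 points | 0.20 × 10.1 = 2.0 points |

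Direct check of the 4.0: intervention (36×0.60 + 24×0.80)/60 = 68%; usual care (24×0.60 + 36×0.80)/60 = 72%.

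**Type I error by simulation.** Null trials, 10,000 per setting, exponential times, censoring at 24 months, independent participants, ordinary log-rank. The planned bootstrap was not simulated, so the rates are indicative.

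| Setting | Unstratified | Stratified by phase |
|---|---|---|
| 36:24 then 24:36, 70% to 80% | 6.1% (5.7% in a separate run) | 5.6% |
| 36:24 then 24:36, 60% to 80% | 7.5% (7.3% to 7.9% across runs) | 4.9% |
| 36:24 then 30:30, 60% to 80% | 5.4% | not needed for the comparison |
| 36:24 then 24:36, no drift | 5.3% | 5.4% |

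A 5-point drift with the reversal gave 5.1%. A more extreme 40:20 then 20:40 with a 20-point drift gives 0.20 × 33.3 = 6.7 points and about 12.8% unstratified, against about 5% stratified.

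**How likely is the trigger?** At 3–4 participants per cluster, the first 60 come from about 60/3.5 ≈ 17 weeks. Treating these as one sequence, simple randomisation gave a 60:40 split or worse in about 41% of sequences; blocks of four gave none. The article does not say which is used.

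**What the correction buys.** Efficiency relative to an equal split is 4p(1−p). At 66:54, p = 0.55 and efficiency is 0.99. At 72:48, p = 0.60 and efficiency is 0.96. A 36:24 first half followed by 30:30 ends at 66:54, so leaving it alone costs about 1%.

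**The case against.** **The drift may be small.** At 3–4 participants per week, 120 participants need 120/4 = 30 to 120/3 = 40 weeks, or fewer if that rate is per site, so the midpoints of the halves lie about 15–20 weeks apart. A 20-point shift in that time equals the whole target effect, and nothing in the article supports it. This stands: the 10-point row is the more cautious one. Enrolment half is also a loose proxy for when the adult visit falls due, since participants aged 16–17 reach it at different times. That blurs drift in clinic capacity.

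**The imbalance may not arise, or be only partly reversed.** This stands too. With blocks of four, the rule gave 4.9% even at a 20-point drift.

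**The strata may be left to the analysis plan.** This stands only in part. The allocation rule is a design decision fixed here, and the article does describe stratified analyses, without phase. It does not exclude a phase-stratified primary test, so the point is a correction to make, not proof that the analysis will be wrong.

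**Stronger readings that a reader might infer.**
- That the rule causes the whole 4 points. It does not: about 2 exist from the first-half imbalance alone.
- That the bias favours one arm. Chance imbalance has no systematic direction.
- That growing nurse experience creates a spurious difference. Nurses deliver only the intervention, so with no true effect their experience cannot do this; it would change the average effect being estimated.
- That re-weighting conceals differential recruitment. The re-evaluation is declared in advance and the trial follows CONSORT, so first-half counts can be reported.

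**Conclusion.** The point holds as a conditional weakness. A stated allocation rule can associate arm with enrolment phase, and the primary test as described does not allow for it. Harm needs both an imbalance that triggers the change and a calendar trend in attendance. For a fully reversed 36:24 first half, the cost is 2 points and about 6% type I error at a 10-point drift, or 4 points and about 7.5–8% at a 20-point drift, against a 20-point target. With no drift, or with no imbalance, there is no inflation.

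The reversal accounts for about half of the spurious difference, but for most of the excess type I error in the 20-point case (5.4% without it, about 7.5% with it). The documents do not support saying that the trial is biased. They support saying that a small, avoidable risk is taken for about 1–4% of precision, and that the remedy is simple.

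**What to change.** Choose one of two routes.

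1. **Keep the option to change the ratio.** State that, if it is used, the primary log-rank will be stratified by site and enrolment phase (before or after the change), that phase will enter the mixed models, and that weeks will be resampled within those strata. Report enrolment by arm and phase. No new data are needed. The main cost is fewer weeks per stratum: 30–40 weeks over four strata is about 8–10 each if the sites enrol equally, so the bootstrap's type I error should be checked by simulation beforehand.
2. **Drop the option.** Randomise weeks 1:1 throughout, in permuted blocks within site, and accept a slightly unequal final split. The cost is a revised randomisation list and about 1% of efficiency at 66:54, or 4% at 72:48.

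If the ratio has already been changed, only the analysis part of the first route is still open. It should be written down before outcomes are compared by arm.
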